## 5 INVESTIGATIONAL MEDICINAL PRODUCTS

### 5.1 IDENTIFICATION AND DESCRIPTION OF INVESTIGATIONAL MEDICINAL PRODUCTS (IMP(S))

#### **Tacrolimus**

TAC is a macrolide calcineurin inhibitor. TAC is indicated for the prophylaxis of organ rejection, in adult and pediatric patients receiving allogeneic kidney, liver transplants and heart transplants, in combination with other immunosuppressants. TAC is approved for its intended use in this clinical study by all national competent regulatory authorities of the participating countries.

In T-cells, activation of the T-cell receptor normally increases intracellular calcium, which acts via calmodulin to activate calcineurin. Calcineurin then dephosphorylates the transcription factor nuclear factor of activated T-cells (NF-AT), which moves to the nucleus of the T-cell and increases the activity of genes coding for IL-2 and related cytokines. TAC prevents the dephosphorylation of NF-AT. In detail, TAC reduces peptidylprolyl isomerase activity by binding to the immunophilin FKBP12 (FK506 binding protein), creating a new complex. This FKBP12–FK506 complex interacts with and inhibits calcineurin, thus inhibiting both T-lymphocyte signal transduction and IL-2 transcription.

#### **TTV R-GENE®**

The TTV R-GENE®, using real-time PCR technology after extraction of the viral DNA, enables to detect and quantify the genome of TTV in whole blood, plasma and serum samples (Kulifaj et al. Journal of clinical virology. 2018; McCulloch et al. 22nd Annual Meeting of the European Society for Clinical Virology, Copenhagen. 2019). The TTV R-GENE® kit is CE certified.

TTV, classified in the Anelloviridae family, is a non-enveloped, single-stranded, and circular DNA virus. TTV is a member of the Alphatorquevirus genus, which includes at least 20 human species. Human Anelloviridae are also represented by the Torque teno mini virus (TTMV) and the Torque teno midi virus (TTMDV), belonging to the Betatorquevirus and Gammatorquevirus genera, respectively. The highly diverse anellovirus family has been identified as one of the main components of the human blood virome; its prevalence is very high, usually more than 90%. Multiple infections with different TTV species are acquired over time, starting early in infancy, and result in lifelong viremia. This virus is transmitted through many channels: blood, oral, fecal, sexual, mother to child, among others. To date, TTV has not been clearly associated with any clinical manifestation and the clinical utility of TTV relies on its relationship with the functional immune status of the individual (De Vlamincx et al. Cell. 2013; Focosi et al. Clinical microbiology and infection. 2016).

### 5.2 SIDE EFFECTS AND INTERACTIONS

The reference safety information is listed in the SmPCs and are provided to the trial site with the investigator site file (ISF). The most common adverse reactions observed in TAC-treated kidney transplant patients are: infection, tremor, hypertension, abnormal renal function, constipation, diarrhoea, headache, abdominal pain, insomnia, nausea, hypomagnesaemia, urinary tract infection, hypophosphatemia, peripheral oedema, asthenia, pain, hyperlipidaemia, hyperkalaemia, and anaemia.

- Patients receiving TAC, are at increased risk of developing lymphomas and other malignancies, particularly of the skin. Post-transplant lymphoproliferative disorder has been reported in immunosuppressed organ transplant recipients. Cases of pure red cell aplasia have been reported in patients treated with TAC.
- Patients receiving TAC are at increased risk of developing bacterial, viral, fungal and protozoal infections, including opportunistic infections. These infections may lead to serious, including fatal, outcomes. Serious viral infections reported include PVAN, mostly due to BK virus infection and CMV infections.
- TAC was shown to cause new onset diabetes mellitus.
- TAC can cause acute or chronic nephrotoxicity. TAC may cause a spectrum of neurotoxicities. The most severe neurotoxicities include posterior reversible encephalopathy syndrome, delirium, seizure and coma; others include tremors, paresthesias, headache, mental status changes, and changes in motor and sensory functions.
- Hyperkalemia has been reported with TAC. Hypertension is a common adverse effect of TAC therapy. TAC may prolong the QT/QTc interval and may cause Torsade de Pointes. Myocardial hypertrophy has been reported.

### 5.3 MANUFACTURING AND LABELLING

Standard TAC packaging/labelling/dosage form as provided by the vendors will be used. There will be no restriction on a certain TAC formulation or vendor/distributor. The TAC containing drug will be obtained as usual by the subjects themselves at their local pharmacies.

### 5.4 STORAGE, DISPENSE, RETURN AND DOCUMENTATION OF INVESTIGATIONAL DRUG (DRUG ACCOUNTABILITY)

Medications are handled according to standard practice. Batch numbers of TAC will be recorded.

### 5.5 ASSIGNMENT OF THE TREATMENT ARM

The assignment of a subject to a treatment arm is done by randomization, see 6.2.

### 5.6 TREATMENT PLAN

All patients will receive TAC based triple immunosuppression according to trial site routine standard. TAC in the active group will be guided by TTV as described in 5.7. There is no restriction to brand/formulation/rout of administration within this trial. TAC will be dosed according to TTV at every study visit up to visit 6. Follow up will end at month 13 post-transplant as detailed in 6.12.

### 5.7 INSTRUCTIONS FOR DOSE ADJUSTMENT

#### Background:

Applying the Vienna in-house PCR an increased risk for allo-graft rejection and infection was described for a TTV load outside of 6 log10 c/ml to 8 log10 c/ml in month 4 to 12 after kidney transplantation (Doberer K et al, American Journal of Transplantation, 2020). Applying this range to all available samples in the cohort described in the above cited publication in the same period, 41% of the measurements were below and 29% above the range. An upper cut-off of 7.6 log10 c/ml scored 38% of the samples above the range and thus leads to a more equal distribution (unpublished data). In preparation for this trial, we re-analysed TTV in the above

mentioned cohort using the Vienna in-house PCR and the PCR applied during the trial - the TTV R-GENE® assay - in parallel (unpublished data). The two assays were highly associated (slope: estimate 0.91, 95% CI 0.89 to 0.93; R 0.91) and the Bland-Altman plot revealed a mean difference of 1.4 log10 c/ml (95% CI of from -2.9 to 0.2). Applying this number the optimal TTV range for the trial was set at 4.6 log10 c/ml to 6.2 log10 c/ml.

### 5.7.1 ACTIVE/INTERVENTION GROUP

#### 5.7.2 MAIN PRINCIPLES

**TTV-guided TAC dosing:** The TAC trough level target will be adapted according to TTV copies per milliliter (c/mL) in the plasma (quantified by TTV R-GENE®) at study visit 1 to 6. The target TTV load ranges from 4.6 log10 c/mL to 6.2 log10 c/mL as defined by TTV R-GENE® (=optimal range). TAC dosing according to TTV is detailed in Figure 3

**1. If TTV is not within the optimal range, the TAC trough level target has to be adapted by one step up or down compared to the current TAC trough level.**

If TTV is below the optimal TTV range, the TAC trough level target has to be increased by one step compared to the current TAC trough level, if TTV is above the optimal TTV range, the TAC trough level target has to be decreased by one step compared to the current TAC trough level.

**2. One TAC trough level adaption step is defined as 2 ng/mL (investigators are allowed to target a range of +/-1 ng/mL; thus one step might be within a minimum of 1 ng/mL and a maximum of 3 ng/mL).**

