### 3.3 SECONDARY END POINTS

- Single components of the primary outcome
- Episodes of infection and graft rejection defined by the treating medical personnel
- Severe infection (necessitating treatment in the inpatient or day-care ward) and severe rejection (excluding BL TCMR)
- All of the three mentioned secondary end-points including COVID-19
- Episodes of infection due to COVID-19
- Estimated glomerular filtration rate (eGFR; current CKD EPI and MDRD abbreviated)
- Rejection detected by protocol biopsy at month 12 post-transplantation: according to BANFF 2019 meeting report (including/excluding BL TCMR) and according to molecular microscope (MMDX)
- *de novo* donor specific antibodies (DSA)

- Plasma TTV load
- TAC trough level and dose
- Unchanged, increased, and decreased TAC trough target levels
- Health related quality of life: SF-36 and MTSOSD-59R questionnaires
- Drug adherence assessed according to paper-based assessment, MEMS® Buttons (AARDEX Group, Switzerland) on TAC blisters, BAASIS questionnaire, claimed prescriptions, psychological evaluation and TAC trough level variability
- Adverse Events and Serious Adverse Events (AEs/SAEs)
- Development of malignoma

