#### Dosing example

The patient has a current TAC trough level of 7.2 ng/mL. The TAC dose has to be adapted to target 5.2 ng/mL TAC trough level (= 4.2 to 6.2 ng/mL range) if the current TTV load is above the optimal range limit of 6.2 log10 TTV c/mL and adapted to 9.2 ng/mL TAC trough level (=8.2 to 10.2 ng/mL range) if the current TTV load is below the optimal range limit of 4.6 log10 TTV c/ml, respectively.

**Figure 3 TAC Dosing According to TTV Range.**[figure not shown]

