### 5.7.3 ADDITIONAL RULES

- **All changes in TAC dose (including all non-study visits) must be performed according to the study protocol and the current TAC trough level target.**
- **TAC adaptations have to be made within 48 hours after the receipt of the TTV load.**
- **The lowest TAC trough level target is 3.5 ng/mL, the highest is 10 ng/mL.**
- **The treating physician can request additional TAC trough levels at any time (also on non-study visits) but TTV load will only be assessed and TAC trough level target changes only performed at the study visits.**
- **If non-adherence is suspected, no increase in TAC trough level target will be performed:** E.g. a failure of TAC intake more than once per week on average for b.d. and once every two weeks on average for o.d. formulation detected by the patient diary. In this case the patient should be educated about medical adherence (e.g. psychological counseling) and the target TAC trough level will not be changed according to TTV load until the next study visit.

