**If the investigator decides to continue, the following rules apply:**

• **Rejection:**

- if TTV load suggests TAC trough level target step down, this suggestion must not be followed and TAC trough level target will be chosen by the investigator (e.g. stay on TAC trough level target or increase TAC trough level target)
- if TTV load suggests no change in TAC trough level target this suggestion may be followed or TAC trough level target may be chosen by the investigator (e.g. increase TAC trough level target)

• **Severe infection:**

- If TTV load suggests TAC trough level target step up, this suggestion must not be followed and TAC trough level target will be chosen by the investigator (e.g. stay on TAC trough level target or decrease TAC trough level target)
- If TTV load suggests no change in TAC trough level target this suggestion may be followed or TAC trough level target may be chosen by the investigator (e.g. decrease TAC trough level target)

• **Relevant BKV infection:**

- If a TAC trough level target step down is indicated by TTV load, a 'reduction of TAC as a treatment response to BKV' is the preferred strategy.
- If no TAC trough level target change is indicated by TTV load, a 'reduction of the antimetabolite as a treatment response to BKV' is the preferred strategy.
- If a TAC trough level target step up is indicated by TTV load, it has to be ignored and a 'reduction of the antimetabolite as a treatment response to BKV' is the preferred strategy.
- Investigators are encouraged not to use a 'switch from mycophenolic acid to azathioprine' as treatment response for BKV.
- Introduction of IVIG is possible independently of the treatment strategy and the TTV load.

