### 6.14 DEVIATIONS FROM THE PROTOCOL

The principal investigator is responsible for ensuring that the clinical trial is conducted at the trial site in accordance with the trial protocol. If there are nevertheless deviations from the valid protocol, specified procedures, GCP and/ or the applicable regulatory requirement(s), these must be documented by the trial site, including a clear description and justification.

Subject-related deviations are documented in the eCRF. Subject-independent deviations are documented on a separate form, which is stored in the ISF.

Deviations from the protocol are e.g.:

|                                                                             | minor | major | critical |
|-----------------------------------------------------------------------------|-------|-------|----------|
| Deviations in relation to the inclusion or exclusion criteria               |       |       | X        |
| Examinations/visits that were missed                                        |       | X     |          |
| Examinations/visits that did not take place within the given time window    | X     |       |          |
| Non-performance of laboratory analyses in regard to TTV-level determination |       | X     |          |
| Non-Adherence in regard to IMP intake                                       |       | X     |          |
| Incorrect administration of the IMP (dosing)                                |       | X     |          |
| Intake of expired IMP                                                       |       | X     |          |

|                                                                                |  |   |   |
|--------------------------------------------------------------------------------|--|---|---|
| Excluded concomitant medication has been taken by the patient                  |  | X |   |
| Treatment not as randomized                                                    |  |   | X |
| Incorrect adjustment of the IMP according to TTV-level in the TTV guided group |  | X |   |
| Deviations that have led to an (S)AE                                           |  | X |   |

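### The tacrolimus step is counted from the measured level but described as a change of a standing target, and its range is not reconciled with the 3.5 to 10 ng/mL limits

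*Protocol*

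**What the plan says.** The rule for the TTV-guided arm is in Protocol section 5.7.2. For a TTV load outside the intended window, it states that "the TAC trough level target has to be adapted by one step up or down compared to the current TAC trough level". On size, "One TAC trough level adaption step is defined as 2 ng/mL", with latitude of 1 ng/mL either way, "thus one step might be within a minimum of 1 ng/mL and a maximum of 3 ng/mL". The section adds that TTV below range means the target goes up and TTV above range means it goes down.

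The dosing example takes a patient whose current trough level, not target, is 7.2 ng/mL. A step down leads to 5.2 (4.2 to 6.2) ng/mL. A step up is "adapted to 9.2 ng/mL TAC trough level (=8.2 to 10.2 ng/mL range".

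Other sections treat the target as a quantity that persists between visits:

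- Section 5.7.3 requires every dose change, including those between study visits, to follow the target then in force, and lets that target change only at study visits. It adds: "The lowest TAC trough level target is 3.5 ng/mL, the highest is 10 ng/mL".
- Section 5.7.4 speaks of lowering or changing the target by 1 ng/mL. In the Visit 1 hint it names level and target as separate things in one sentence.
- Section 5.7.5 begins a rule with "if TTV load suggests TAC trough level target step down" and lets the investigator keep the existing target or raise it.
- Section 3.3 lists a secondary endpoint, "Unchanged, increased, and decreased TAC trough target levels".

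Section 6.14 grades "Incorrect adjustment of the IMP according to TTV-level in the TTV guided group" as a major deviation.

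**The concern.** Raising a target and setting it to the measured level plus one step are the same instruction only when the patient sits exactly on target. Off target, the text supports two different new targets, and section 5.7.2 can call a lower target an increase. Separately, the step range and the target limits are stated without saying how they combine, and the one example given runs past a limit.

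This rule is the tested intervention. If it can be read in two ways, two sites may set different targets for the same patient. Whether an adjustment counts as incorrect under section 6.14, and whether the secondary endpoint records an increase, a decrease or no change, then depends on the reading. The trial would also be harder to replicate from its protocol.

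**Working it through.** **Inputs.** Nominal step 2 ng/mL and permitted step 1 to 3 ng/mL (section 5.7.2); example level 7.2 ng/mL (dosing example); target limits 3.5 and 10 ng/mL (section 5.7.3). The standing target of 7 ng/mL used in step 3 is an assumption, because the document gives no single one.

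**1. Reproduce the example.** New target = level ± step.

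| Step (ng/mL) | Down from 7.2 | Up from 7.2 |
|---|---|---|
| 1 | 6.2 | 8.2 |
| 2 | 5.2 | 9.2 |
| 3 | 4.2 | 10.2 |

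All six values match the example, so it does count from the measured level. Five lie within 3.5 to 10. Only 10.2 does not, by 10.2 − 10 = 0.2 ng/mL.

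**2. Where step and limits collide.** A step up of size s passes the upper limit when level > 10 − s. A step down passes the lower limit when level < 3.5 + s.

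| Step (ng/mL) | Up exceeds 10 if level is above | Down falls below 3.5 if level is below |
|---|---|---|
| 1 | 9.0 | 4.5 |
| 2 | 8.0 | 5.5 |
| 3 | 7.0 | 6.5 |

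Every permitted step fits in both directions only for levels of 6.5 to 7.0 ng/mL. If the limits act as a cap, a shortened step still works in most cases. For a step up from above 9, or a step down from below 4.5, the room left is under the 1 ng/mL minimum, so both statements cannot be obeyed. For a step up from above 10, any target within the limits lies below the measured level.

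**3. The two reference values.** From the level L the new target is L ± s; from the standing target T it is T ± s. The difference is L − T whatever the step. Counting from the level, a step up lowers the target when T − L > s, and a step down raises it when L − T > s. With T = 7 (assumed) and s = 2:

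| Level | TTV asks for | From level | From target | Target change, counting from level |
|---|---|---|---|---|
| 4 | up | 6 | 9 | falls by 1 |
| 5 | up | 7 | 9 | none |
| 9 | down | 7 | 5 | none |
| 10 | down | 8 | 5 | rises by 1 |

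All these values lie within 3.5 to 10, so the limits do not remove the discrepancy.

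**4. How often: illustration only.** Assume troughs normally distributed around a target of 7 with coefficient of variation CV. The chance that a step lands on the wrong side of the old target is 1 − Φ(s / (7 × CV)).

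| CV | Step 2 | Step 1 |
|---|---|---|
| 15% | 2.8% | 17.0% |
| 20% | 7.7% | 23.8% |
| 30% | 17.0% | 31.7% |

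The target, the CV and the normal shape are all assumptions.

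**5. Power.** The stated power is Φ(0.2 / √(0.21/120 + 0.24/120) − 1.96) = 0.9042, which matches the protocol's 90.42%. Nothing in the dosing rule enters it.

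**The case against.** The strongest reply is that only one reference value is ever stated. Section 5.7.2 gives it twice, the example applies it, and no section says in words that the step is counted from the previous target. Section 5.7.3 tells sites which target to dose towards between visits, section 5.7.5 uses step terms already defined, and section 5.7.4 can be taken as loose wording about step size. Figure 3, which section 5.7.2 cites for the detail, is not available here and may settle the question. Measured against the patient's actual level, the rule moves in the direction TTV asks for: from a level of 10, a new target of 8 is a reduction. The limits appear among additional rules and can be read as a cap. Section 5.7.7 also bars dosing on levels that are not at steady state, and patients without stable troughs are excluded.

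Much of this stands. The target-based reading is implied, not stated, and the example breaks one limit at one edge only. But section 5.7.2 itself orders the target to be raised or lowered, and its own formula can do the opposite. The steady-state rule does not help with a genuine steady-state level that is off target. A cap leaves open what happens when less than 1 ng/mL of room remains. A clear Figure 3 would still leave the text to be aligned with it.

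A reader might infer more than the documents support:

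- **That sites will deliver different interventions.** This is a risk, not something shown, and the 1 to 3 ng/mL latitude is deliberate.
- **That affected patients drop out of the per-protocol set.** Section 10.3.1 removes only those whose critical or major violation might affect evaluation of the primary objective.
- **That about 600 decisions are at stake.** The background to section 5.7 gives 41% of samples below and 38% above range, and 0.79 × 6 visits × 130 patients = 616. Those shares come from an observational cohort without TTV guidance, on a different PCR, so they are not a forecast for this arm.

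**Conclusion.** The rule is wrong as written, in a limited form. Section 5.7.2 and its example count the step from the measured level but describe it as a change of the target, which sections 5.7.3, 5.7.4 and 5.7.5 treat as a standing quantity. The resulting targets differ by level minus target, and the direction of the target change reverses once that gap exceeds the step. The example exceeds the maximum target by 0.2 ng/mL at one edge. Above 9 ng/mL (step up) and below 4.5 ng/mL (step down), the limits and the minimum step are incompatible.

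These results are arithmetic on the protocol's own figures, except that the numerical reversals use an assumed target of 7 ng/mL. How often a reversal would occur cannot be taken from the document; the 2.8% to 31.7% range only illustrates it.

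What depends on the reading is the definition of the intervention, the incorrect-adjustment deviation and the target-change endpoint. The primary analysis follows randomised allocation in the modified intention-to-treat set, with per protocol as a sensitivity analysis. The primary test and the power are not affected.

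**What to change.** Reconcile sections 5.7.2 (with its example and Figure 3), 5.7.3, 5.7.4 and 5.7.5 so that:

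- one reference value for the step is named and used throughout;
- the text says how the step size and its latitude behave near the two limits, including when less than the minimum step is available;
- the example agrees with the result.

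Which reference value and which limits apply is for the sponsor's clinicians, and nothing here favours one.

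At each of visits 1 to 6, record the old target, the reference value used and the new target, if the eCRF does not already do so. Derive both the target-change endpoint and the incorrect-adjustment deviation from those fields, so that they share one definition.

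The cost is a wording change, a corrected example, a small eCRF addition and a short retraining note to sites. The sample size and the primary analysis stay as they are.

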#### Dosing example

The patient has a current TAC trough level of 7.2 ng/mL. The TAC dose has to be adapted to target 5.2 ng/mL TAC trough level (= 4.2 to 6.2 ng/mL range) if the current TTV load is above the optimal range limit of 6.2 log10 TTV c/mL and adapted to 9.2 ng/mL TAC trough level (=8.2 to 10.2 ng/mL range) if the current TTV load is below the optimal range limit of 4.6 log10 TTV c/ml, respectively.

**Figure 3 TAC Dosing According to TTV Range.**[figure not shown]

